## Abstract

**Background:**

Reverse total shoulder arthroplasty (RTSA) has emerged as a successful surgery with expanding indications. Outcomes may be influenced by post-operative rehabilitation; however, there is a dearth of research regarding optimal rehabilitation strategy following RTSA. The primary purpose of this study is to compare patient reported and clinical outcomes after RTSA in two groups: in one group rehabilitation is directed by formal, outpatient clinic-based physical therapists (PT group) as compared to a home therapy group, in which patients are instructed in their rehabilitative exercises by surgeons at post-operative appointments (HT group). Secondary aims include comparisons of complications, cost of care and quality of life between the two groups.

**Methods:**

This randomised controlled trial has commenced at seven sites across the United States. Data is being collected on 200 subjects by clinical research assistants pre-operatively and post-operatively at 2, 6, and 12 weeks, 6 months, 1 and 2 year visits. The following variables are being assessed: American Shoulder and Elbow Surgeons (ASES), pain level using the numeric pain scale, the Single Assessment Numeric Evaluation (SANE) score, and shoulder active and passive range of motion for analysis of the primary aim. Chi square and t-tests will be used to measure differences in baseline characteristics of both groups. Repeated measures linear mixed effects modeling for measurement of differences will be used for outcomes associated with ASES and SANE and scores, and range of motion measures. Secondary aims will be analyzed for comparison of complications, cost, and quality of life assessment scores using data obtained from the PROMIS 29 v. 2, questionnaires administered at standard of care post-operative visits, and the electronic health record. Subjects will be allowed to crossover between the PT and HT groups, and analysis will include both intention-to-treat including patients who crossed over, and a second with cross-over patients removed, truncated to the time they crossed over.

**Discussion:**

RTSA is being performed with increasing frequency, and the optimal rehabilitation strategy is unclear. This study will help clarify the role of formal physical therapy with particular consideration to outcomes, cost, and complications. In addition, this study will evaluate a proposed rehabilitation strategy.

**Trial registration:**

This study is registered as NCT03719859 at ClincialTrials.gov.

**Supplementary Information:**

The online version contains supplementary material available at 10.1186/s40945-021-00121-2.

## Background

Growing acceptance of the expanding indications and the success of reverse total shoulder arthroplasty (RTSA) has led to a dramatic increase in shoulder arthroplasty in the United States [1]. Between 2011 and 2017 the number of RTSA surgeries in the United States increased 191.3% with 63,845 procedures performed in 2017 [2]. Initially used only for cuff tear arthropathy, [3, 4] RTSA is now frequently employed for a wider variety of shoulder pathologies including proximal humerus fractures, rheumatoid arthritis, osteoarthritis (OA), tumors, avascular necrosis, and massive rotator cuff tears without arthritis [3, 5–8]. The RTSA prosthesis is effective at providing improved active motion and function due to the semi-constrained design. This design substitutes for the centering effect of the deficient rotator cuff and allows the deltoid to elevate or abduct the arm with fixed-fulcrum kinematics [9, 10]. Many factors are hypothesized to influence the potential for a successful outcome following RTSA: proper patient selection, surgeon expertise, prosthetic design, surgical technique and approach, and post-operative rehabilitation [11–13]. Whilst prior researchers have explored the effect of surgical technique, type of prosthesis and surgical indications on outcome following RTSA, [14] there is limited literature on the influence of post-operative rehabilitation on outcomes. The surgical procedure is often reserved for an elderly population who are at least 65 years of age, [15] and a younger age is a risk factor for post-operative complications [16].

Dating back to the work of Hughes and Neer, [17] a proper rehabilitation strategy has been felt to be imperative following shoulder arthroplasty. Early range of motion in a protected and graduated way has been proposed to avoid stiffness and muscle atrophy whilst also protecting healing tissues, and avoiding complications such as instability and stress fractures [17–26]. There are multiple published rehabilitation protocols for both anatomic total shoulder arthroplasty (ATSA) and RTSA, which include thorough biomechanical rationales [17–26]. However, as Bullock et al. reported in a recent systematic review of proposed rehabilitation guidelines, there is nominal consensus regarding rehabilitation strategies, and there is a need for high-quality prospective research [27]. Currently, there are only four published studies on therapy after ATSA [24, 28–30], and two published studies evaluating the rehabilitative strategy for RTSA [31, 32]. One prospective ATSA [28] and two prospective RTSA [31, 32] studies report on the impact of immediate versus delayed therapy, and all conclude that there is overall no significant difference in clinical and patient reported outcomes. Three retrospective studies [24, 29, 30] report on outcomes for therapy after ATSA, with one study concluding that home therapy directed by the surgeon had favorable outcomes compared to formal physical therapy [29]. A retrospective case series demonstrated successful range of motion and patient reported outcomes following ATSA when rehabilitation was conducted at home using web-based exercises generated and provided by the surgeon [30]. There are no published randomised controlled trials comparing home therapy to formal physical therapy following RTSA.

There is nominal consensus on the optimal therapy protocol following RTSA, or on who should instruct and supervise rehabilitation [33]. The only consensus is that therapy is felt to play an important part in RTSA outcomes and that there is a need for research to guide this clinical question [27, 33]. Authors universally note the unsettling discrepancy between “doing nothing” [18] and a formal protocol involving multiple outpatient or even inpatient visits. This discrepancy in service provision suggests a need for a well-designed randomised trial [27, 33]--especially given the cost associated with the latter strategy [18, 29].

We aim to compare outcomes for formal, clinic-based physical therapy (PT group) to home therapy, in which patients are provided with instructions from surgeons at post-operative appointments (HT group) by using a superiority, randomised design [34]. Findings will aid in determining the potential role of formal PT in the RTSA recovery process, and secondarily, will evaluate a formal RTSA rehabilitation protocol, which is standardized for the trial [20].. Findings from the study may assist in evaluating the financial benefit or burden of formal PT in the RTSA recovery process and determine the resource necessity of PTs in a traditional clinical environment. We hypothesize that the PT group will demonstrate superior clinical and patient reported outcomes, significantly quicker levels of recovery, and significantly higher levels of overall recovery at our long-term outcomes capture when compared to the HT group. Secondary aims of this project include analysis of the incidence of complications between the two groups, specifically acromial stress fractures and prosthetic instability events, which we hypothesize will be higher in the PT group; and cost of care which we hypothesize will be higher in the PT group.

## Methods

### Study design

This is a multicenter, prospective, randomised controlled trial with parallel groups evaluating patients who have RTSA at one of the participating sites by a shoulder fellowship-trained American Shoulder and Elbow Surgeons member. These surgeons have specialized training in shoulder surgery including the RTSA procedure. This protocol was created using the Standard Protocol Items, Recommendations for Interventional Trials (SPIRIT) reporting parameters [35]. A checklist demonstrating compliance with the SPIRIT parameters is included as supplemental material. This study was prospectively registered as NCT03719859 at ClincialTrials.gov. The study is externally funded by the Orthopedic Research and Education/The Aircast Foundation grant number 18–058. The role of this funding source is solely financial and not influential or contributory to the design of the protocol or interpretation of results.

### Research ethics approval

A full non-expedited Institutional Review Board approval of this study was provided on 8.17.20 (ORA: 18082102-IRB01) at the lead institution (Rush University Medical Center) including a patient informed consent form. A full Institutional Review Board approval also is required for each participating site. The approved informed consent form which is being used at the lead research site (Rush University Medical Center) is included in the Supplemental materials. Any changes to the research protocol will need approval by the IRB for all sites.

### Eligibility criteria/subjects

Participants are identified as potential subjects for this study if they are over 50 years of age, under the care of one of the participating surgeons, and elect to have RTSA for rotator cuff tear arthropathy, massive irreparable rotator cuff tear, or primary osteoarthritis. Subjects are excluded from study participation for the following reasons: history of prior ipsilateral open shoulder surgery, non-reverse total shoulder arthroplasty, RTSA for fracture or revision arthroplasty, RTSA with a tendon transfer, discharge to a skilled nursing facility, in-patient rehabilitation placement, or use of home health therapy prior to progressing in recovery, unwilling to make a good faith effort to adhere to their randomly prescribed rehabilitation scheme, unable to speak, read, or write the English language, have cognitive deficits limiting ability to follow direction, unable or unwilling to be randomised due to financial or personal constraints, or have inability to attend physical therapy (i.e. transportation or financial limitations). Subjects who meet the inclusion criteria are identified at clinical appointments with participating surgeons, and clinical research assistants discuss the study process and review the voluntary informed consent process. At this appointment the following variables are obtained as pre-operative baseline values: American Shoulder and Elbow Surgery (ASES) score, Numeric Pain Rating Scale (NPRS) level, Single Assessment Numeric Evaluation (SANE) score, active range of motion (AROM), passive range of motion (PROM), and Patient-Reported Outcomes Measurement Information System (PROMIS) score. Upon voluntary consent to participate, clinical research assistants employ computer based Research Electronic Database Capture (REDCap) (Nashville, TN) [36] to perform the allocation sequencing of subjects to either the PT or HT group. The randomization schedule is a randomized block design stratified by site using a 1:1 treatment allocation in blocks of size 8.. Patients are encouraged to remain within the group to which they are randomly assigned for the duration of the study, however, if the patient, surgeon, or therapist has concern regarding patient safety, compliance or outcome due to the group assignment, cross-over to the other group will be allowed. The research plan is for approximately a 15% crossover rate based on prior research which planned for 10%, but actually ended up with 30% crossover [37]. The reason for cross-over will be recorded in the electronic health record and reported in the study result.

Patients who participate in this project are offered $25 gift cards at the 6 month office visit to thank them for their participation and encourage study retention.

All study patients are treated with an RTSA using a deltopectoral approach. Different implant systems are being utilized at the discretion of the treating surgeon based on their preferred implant. To assess for potential confounding variables, implant characteristics which might affect range of motion, stability, and potential for acromial stress fractures are captured including: implant manufacturer, implant model, glenosphere center of rotation from the glenoid face (recorded in millimeters), glenosphere diameter, and polyethelene liner thickness.

All patients in the study attend post-operative appointments with their surgeon at 2 and 6 weeks, 3 months, 6 months, 1 and 2 years according to standard of care. These are the same intervals at which data is collected by clinical research assistants.

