### Interventions

#### Rehabilitation management

##### Physical therapy and home therapy groups

Prior to discharge from the hospital or surgical center, all subjects in both study groups (PT or HT) receive the same phase 1 exercise instruction by occupational or physical therapists. Patients in the PT and HT groups follow the rehabilitation guidelines proposed by Boudreau et al. [20] which are detailed in Table 1.

**Table 1 Tab1:** Rehabilitation guidelines for reverse total shoulder arthroplasty

PHASE	PRECAUTIONS AND GUIDELINES	GOALS	EXERCISES	CRITERIA TO ADVANCE TO NEXT PHASE
1 (post-op day 1-2 week)	Sling 24/7 (remove for grooming and HEP-3 5x/day) Avoid hand behind back, and reaching cross body Keep arm anterior frontal plane “always see elbow” No shoulder AROM No submersion in water No weight bearing on shoulder	Protect prosthesis from dislocation Prevent infection Promote distal circulation Proper sling fit PROM: 120 elevation and 30 ER	Pendulum Active elbow, wrist and hand, scapular retraction Passive elevation to 90-120 deg in scapular plane Passive ER to 30 deg inscapular plane	Pain less than 3/10 with PROM Healing incision without signs of infection Clearance by MD after radiograph assessment at 2 week check up
2 (3-6 wks)	Sling only in community Use of operative arm allowed for basic ADLs with elbow beside waist – nothing heavier than a coffee cup. No active reaching from shoulder May submerge in water (eg pool or hot tub) after 4 weeks Continue no shoulder extension, hand behind back, cross body or weight bearing	Passive elevation to 120; ER to 30 Able to fire all heads of deltoid Pain < 3/10	Discontinue elbow, wrist, and hand exs since using arm of ADLs Continue pendulum, scapular retraction, PROM for elevation and ER 120/30 in scapular plane ADD: deltoid isometrics for all heads (avoid extension beyond frontal plane) Reverse pendulum at 90 deg elevation in supine	Passive elevation to 120 and ER to 30 degrees Able to fire all heads of deltoid without pain Able to place and hold arm at 90 deg in supine (balanced position)

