##### Physical therapy intervention group

Subjects in the PT group will begin out-patient clinic-based rehabilitation 4–5 days after discharge from the hospital and continue in therapy approximately once a week for three months. Physical therapists will employ a pragmatic approach within the rehabilitation guidelines summarized in Table 1. Physical therapists will determine the optimal exercises for each patient within the specified guidelines for each phase of recovery. The exercises may vary amongst subjects considering patient specific variables such as exercise tolerance and pain response, ease of progressing to next level of challenge, ability to follow directions and perform exercises correctly, and individual goals for rehabilitation. The number of physical therapy visits may vary amongst patients in this group depending on response to therapy. For example, patients with low demand goals for rehabilitation and/or those who tolerate therapy well and advance easily may need less PT visits than patients with high demand goals and/or those who don’t tolerate therapy well and progress more slowly.

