Clinical research assistants are not blinded due to the need to facilitate appropriate group assignments therefore they are aware of patient group assignment (PT vs HT). Patients are not blinded to group assignment due to their awareness of the rehabilitation occurring at either a physical therapy clinic in weekly appointments or at routine post-operative appointments with the surgeon. For subjects in the PT group, clinical research assistants arrange physical therapy appointments at the appropriate follow-up and ensures the physical therapist is trained with the protocol. For subjects in the HT group, clinical research assistants facilitate the progression of exercises that are taught by the surgeons at the post-operative standard of care appointments during the first 3 months of follow-up. Surgeons and clinical research assistants are trained in the HT exercise progression provided in the pre-printed exercise sheets. For both groups, clinical research assistants obtain the patient reported outcome measures, range of motion measures, and collect patient data regarding compliance, cost, and complications.

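### Exclusions settled at or after hospital discharge are applied to patients allocated on pre-operative consent, which conflicts with the promised intention-to-treat analysis

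*Protocol article*

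**What the plan says.** All the enrolment text is in Eligibility criteria/subjects of the Protocol article.

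- **Enrolment visit.** Patients are identified and consent is discussed at a clinic appointment. "At this appointment the following variables are obtained as pre-operative baseline values".
- **Allocation.** It follows consent: "Upon voluntary consent to participate, clinical research assistants employ computer based Research Electronic Database Capture (REDCap" and so on, to carry out the allocation.
- **Exclusions.** The list opens with "Subjects are excluded from study participation for the following reasons" and includes "discharge to a skilled nursing facility, in-patient rehabilitation placement, or use of home health therapy prior to progressing in recovery". It does not separate a failure at screening from a criterion met after allocation.

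Elsewhere in the article:

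- **Blinding** (Costs and complications data). "Patients are not blinded to group assignment due to their awareness of the rehabilitation". The research assistants are also unblinded.
- **Care before discharge** (Physical therapy and home therapy groups). "all subjects in both study groups (PT or HT) receive the same phase 1 exercise instruction".
- **Care after discharge.** PT patients "will begin out-patient clinic-based rehabilitation" 4–5 days after leaving hospital (Physical therapy intervention group). HT patients continue their hospital exercises until they see the surgeon at about 2 weeks (Home therapy group).
- **Analysis population** (Abstract; Data analysis primary outcomes). Intention to treat is promised, but described only by its retention of patients who cross over.

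**The concern.** An eligibility criterion should be decidable before a patient is randomised. On the plain reading these three are not: discharge destination is settled at discharge, and home health use comes later still. A patient who meets one has normally already been allocated, so applying the criterion takes a randomised patient out of an open-label comparison.

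Two things are at stake. First, intention to treat no longer means all patients as randomised. The article is also uneven here: a patient who moves to the other arm stays in that analysis, while one who uses home health therapy is excluded from participation. Second, if removal differs by arm and those removed recover differently from the rest, the PT–HT difference is biased. The route is clearest for home health use, because an HT patient who struggles in the first two weeks has no planned contact, while a PT patient is already seeing a therapist.

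**Working it through.** **Order of events, from the text**

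1. Pre-operative appointment: consent discussed, baseline values taken.
2. Consent, then allocation through REDCap.
3. Surgery, with the same phase 1 instruction in both arms before discharge.
4. Discharge: nursing-facility or in-patient placement becomes known.
5. After discharge: home health therapy may be used. PT starts at 4–5 days; HT first sees the surgeon at about 2 weeks.

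The three criteria mature at steps 4 and 5, after step 2.

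**The plan's own enrolment figure** (Sample size)

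158 × 0.15 = 23.7, rounded to 24; 158 + 24 = 182. This reproduces the stated 182. The whole allowance is for cross-overs, with none for these exclusions. The Abstract gives 200 subjects, and the extra 18 are not explained.

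**Numbers that could be lost**

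No rate is given, so the rates below are assumptions applied to 182.

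| Removed | Patients lost | Left of 182 | Randomised to retain 182: 182/(1 − rate) |
|---|---|---|---|
| 2% | 3.6, about 4 | 178 | 186 |
| 5% | 9.1, about 9 | 173 | 192 |
| 10% | 18.2, about 18 | 164 | 203 |

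With cross-overs kept in, all three remain above 158. If the 24 cross-overs are also taken out, 154, 149 and 140 remain, all below 158.

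**Possible shift in the PT–HT difference**

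Let p be the share removed in an arm and g the number of ASES points by which those removed score below those kept. The mean of all randomised patients equals the mean of those kept minus p × g, so removal raises the observed arm mean by p × g. Therefore:

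shift in (PT − HT) = (p_PT − p_HT) × g

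Both p and g are assumed; the documents give neither.

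| HT removed | PT removed | g = 10 | g = 15 | g = 20 |
|---|---|---|---|---|
| 5% | 5% | 0 | 0 | 0 |
| 5% | 0% | −0.5 | −0.75 | −1.0 |
| 10% | 5% | −0.5 | −0.75 | −1.0 |
| 10% | 2% | −0.8 | −1.2 | −1.6 |
| 10% | 0% | −1.0 | −1.5 | −2.0 |

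The planned 12-month difference is 79 − 69 = 10 points, so the largest shift shown is 2/10 = 20% of it. The negative sign (a result that flatters HT) follows from assuming more removals in HT. If more PT patients were removed, the sign would reverse.

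**The case against.** The best defence is that the article does not say these patients leave the analysis. It uses an ordinary eligibility list, promises intention to treat, and may leave the handling of late ineligibility to a fuller document. Allocation timing is also inferred: consent gives an order, not a date, and the flow diagram is not shown. Some placements may be planned before surgery and could be screened out properly.

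Much of this stands as a limit on the claim. It does not remove the conflict, because the article itself makes events at or after discharge grounds for exclusion from participation, and nothing shown places allocation later or keeps such patients in. This is a stated rule, not just missing detail.

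A reader might infer more than the documents support:

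- **That removal does differ by arm.** No data show it. For nursing-facility or in-patient placement the route is weak, since instruction before discharge is the same in both arms. Home health use is the plausible one.
- **That tendon transfer and non-reverse implants raise the same problem.** Inclusion already requires electing the reverse procedure, and nothing shows that a tendon transfer cannot be planned beforehand.
- **That the fixed block size makes this worse.** Allocation is "stratified by site using a 1:1 treatment allocation in blocks of size 8", but that bears on predicting future allocations, not on removing randomised patients. It is not part of this point.
- **That the sample size fails.** At 10% loss with cross-overs retained, 164 still exceeds 158.

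**Conclusion.** The concern holds in a limited form. As written, criteria met at or after discharge remove patients already randomised in an open-label trial, and this cannot be squared with the promised intention-to-treat analysis. It rests on reading allocation as pre-operative, which the text supports and nothing shown contradicts.

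Dependence on arm is a risk and not a documented fact. With 0–10% removed per arm and a deficit of 10–20 points in those removed, the shift runs from 0 (equal removal) to about 2 ASES points; the true size and direction cannot be known from the documents. Even the upper figure would not by itself overturn a 10-point effect. The point should be corrected because the bias is avoidable, and it does not invalidate the design.

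**What to change.** 1. State that the discharge-destination and home-health criteria apply only to what is known before allocation.
2. Keep every randomised patient in follow-up and in the intention-to-treat set, whatever the discharge destination or later home health use. This needs no change in sample size.
3. Report these events by arm.
4. Confine any analysis that removes such patients to a sensitivity analysis.

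These changes take a few sentences, plus the IRB approval that the article requires for protocol changes at all sites. They help even though the trial has commenced.

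Where feasible for remaining patients, the allocation could be released at discharge. Care up to then is the same in both arms, and PT starts some days later, so no assigned treatment would change. This would settle discharge destination before allocation, but not later home health use, so item 2 is needed in any case. The cost is a changed REDCap step, IRB approval, and less time to book PT and make sure the therapist is trained, which is harder when the patient's therapist is remote from the site.

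### A single published block size of 8 within each site lets anyone who tracks a site's allocations deduce up to one in five in advance; randomly varied, undisclosed block sizes would remove nearly all of that certainty.

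*Protocol article*

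**What the plan says.** The protocol article, under Eligibility criteria/subjects, sets the schedule as "a randomized block design stratified by site using a 1:1 treatment allocation in blocks of size 8". It mentions no variation in block size and does not say that the size is kept from the sites.

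The same section describes how patients enter. "Subjects who meet the inclusion criteria are identified at clinical appointments with participating surgeons", after which "clinical research assistants discuss the study process and review the voluntary informed consent process". Once the patient consents, the research assistants carry out the allocation in REDCap.

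The paragraph on blinding, after the complications table under Costs and complications data, states: "Clinical research assistants are not blinded due to the need to facilitate appropriate group assignments therefore they are aware of patient group assignment". It adds that they arrange visits for the physical therapy (PT) group, support exercise progression in the home therapy (HT) group, and collect the outcome measures in both.

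Several exclusions leave room for judgement: "unwilling to make a good faith effort to adhere to their randomly prescribed rehabilitation scheme", "have cognitive deficits limiting ability to follow direction" and "unable or unwilling to be randomised due to financial or personal constraints".

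**The concern.** In a permuted block of known size, once one arm has used its quota every remaining place goes to the other arm. Computer allocation can keep the forthcoming list out of view, but it cannot hide past assignments from staff who made them and then arrange the treatment. If those staff also know the block size, they need only count.

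Someone who expects a particular arm next could delay a consent discussion, present the study differently, or read a judgement-based exclusion more or less strictly. The exclusions at issue concern adherence, comprehension and personal constraints, which plausibly bear on ASES, SANE, pain and motion. The Background section hypothesises that PT is superior, so staff may not be indifferent. Selection of this kind would make the arms differ before treatment begins, and the intention-to-treat comparison depends on that not happening.

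**Working it through.** The article gives no predictability figure, so there is none to reproduce.

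**Inputs.** Block size 2m = 8, so m = 4 per arm, and stratification by site (Eligibility criteria/subjects). Seven sites (Abstract). Planned enrolment of 182 (Sample size) or 200 (Abstract). Enrolment per site is not given. An even split is assumed: 182/7 = 26, and 200/7 = 28.6, taken as 28.

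**Certain allocations in a complete block.** There are C(8,4) = 70 equally likely blocks. An allocation is certain when one arm is already used up:

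| Place in block | Blocks where it is certain | Probability |
|---|---|---|
| 1 to 4 | 0 of 70 | 0% |
| 5 | 2 of 70 | 2.9% |
| 6 | 10 of 70 | 14.3% |
| 7 | 30 of 70 | 42.9% |
| 8 | 70 of 70 | 100% |

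The sum is 112/70 = 1.6 per block, which agrees with the closed form 2m/(m+1) = 8/5. As a share, 1.6/8 = 20%.

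**Best guess.** An observer who always guesses the arm with more places left is right on average m + 2^(2m−1)/C(2m,m) − 1/2 = 4 + 128/70 − 0.5 = 5.33 times in 8, or 66.6%, against 50% with no information.

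**Incomplete last blocks.** With 26 patients a site fills three blocks and two places of a fourth. Those two places are never certain, so the share is 3 × 1.6/26 = 4.8/26 = 18.5%. Over seven sites that is 7 × 4.8 = 33.6 of 182. With 28 per site it is 4.8/28 = 17.1%.

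**Varied block sizes.** Simulation at 26 patients per site. The observer sees every allocation in order and knows the set of possible sizes, but not which was drawn:

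| Block sizes | Certain | Best guess correct |
|---|---|---|
| 8 only | 18.5% | 65.6% |
| 8, 10, 12 at random | 1.7% | 63.9% |
| 4, 6, 8 at random | 2.3% | 67.3% |

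Repeat runs moved these by about 0.1 percentage point. Mixing in small blocks removes certainty but makes guessing slightly easier than it is now, so the larger mix is preferable. At 1.7%, about 3 of 182 allocations would be certain (0.017 × 182 = 3.1).

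**The case against.** A reader might infer four stronger things, and the article does not support them.

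- **That the research assistants screen patients.** They are named for the study discussion, consent and allocation. Identification takes place at the surgeons' appointments, and no role is named as applying the exclusions. Several exclusions also rest largely on what the patient declares. What stands is that the assistants take part in the consent discussion, which gives some scope for influence.
- **That one allocation in five is actually known in advance.** The assistants know their patients' groups, but nothing says that any one of them sees every allocation at a site in order. Nor does the article say when, or whether, site staff learned the block size; it only publishes it. The 20% is therefore a ceiling for a fully informed observer.
- **That concealment has failed.** Allocation is computer-based and follows consent. The protocol also permits cross-over after allocation for concerns about safety, compliance or outcome, so staff worried about an assignment have an open route and less reason to steer beforehand.
- **That no analysis could help.** Baseline ASES, pain, SANE, motion and PROMIS are collected, and Data analysis primary outcomes describes a mixed model that can control for baseline differences. Measured imbalance can be addressed. Unmeasured motivation cannot.

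It is also fair to object that varied blocks lower best-guess accuracy by less than 2 percentage points. That stands: the gain lies in removing certainty, and guessing better than chance would persist.

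**Conclusion.** The point holds as a minor design weakness. A single published block size, stratification by site, open treatment, and unblinded staff who handle both consent and allocation together make the ends of blocks predictable. The size is at most 20% of allocations deducible with certainty in complete blocks, and about 17% to 18% if enrolment is spread evenly over seven sites. These figures assume an observer who knows the block size and follows a site's allocations in order from the start of each block; with less information the share is lower.

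The article shows a risk of selection bias and no evidence that any has occurred. The trial had already commenced when the article was written, and the number of allocations still to be made is not stated, so the benefit of a change depends on how many remain.

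**What to change.** For all remaining allocations, replace the fixed block size under Eligibility criteria/subjects with wording such as: allocation is 1:1 and stratified by site, from a list prepared centrally with randomly varied block sizes that are not disclosed to site staff. Sizes of 8, 10 and 12 would serve; the sizes actually used should be left out of documents the sites can read until enrolment closes.

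The cost is a new REDCap allocation table and a short amendment, which under Research ethics approval needs IRB approval for all sites. The largest possible imbalance within a site at the end of enrolment rises from 4 (half of 8) to 6 (half of 12). Any block left incomplete at the switch can add up to 4 more in that site. No analysis model or sample size needs to change.
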